#### Economic Analysis

The principal method will be cost-effectiveness analysis. We will use established methods for comparing costs and changes in scores of dementia specific quality of life instruments between the control and intervention groups [36]. There is a useful opportunity for secondary cost-utility analysis, more exploratory because estimating the utilities of people with dementia is neither easy nor very precise. To complete the picture, we plan to describe all costs and effects for people with dementia and their carers in a cost-consequence analysis.

#### Cost data

This analysis takes a public sector perspective spanning the NHS (dementia services, primary and secondary care) and local government. The interventions received will be fully costed from the perspective of local dementia services to generate a total programme cost and cost per participant-carer pair.

The measurement of health service use is the first step in estimating costs in economic evaluation. We shall estimate the costs of dementia care through the validated CSRI, completed by the family care-giver. There is a growing literature to support the reliability of patient recall as an alternative to GP records [e.g. [37] and our economic protocol is consistent with that used by previous trials in this field [33,34]. GP and other provider records are not an entirely accurate source of service use and hence costing information. These formal records, though mainly computer-based, are often incomplete or difficult to link between primary and secondary NHS care, and social services. So collecting data from GPs and other care providers for the whole sample would add little to the reliability of use and cost information in the planned evaluation. Nevertheless we propose to compare self-reported visits to primary and secondary care over the study period by a sample of 40 participants (20 experimental and 20 controls) with the corresponding GP notes to estimate systematic differences in reports. As the difference in costs and effects between groups is of primary interest, it is especially important to treat these groups identically when costing.

We shall use national unit costs [38,39] to convert service use to monetary costs, including:

• costs of running the joint reminiscence groups;

• costs of reminiscence-based maintenance groups following the initial intervention;

• direct costs of all health care used by participants in the intervention and control arms of the study, including contacts with GPs and practice nurses at home, in surgery or by phone, prescribing and outpatient and inpatient attendances); and

• indirect costs of lost productivity and care-givers attending group sessions;

but not intangible costs.

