**Design and methods:**

This multi-centre, pragmatic randomised controlled trial (RCT) to assess the effectiveness and cost-effectiveness of joint reminiscence groups for people with dementia and their family care-givers has two parallel arms – an intervention group and a control group who receive care as usual. The intervention consists of joint reminiscence groups held weekly for twelve consecutive weeks, followed by monthly maintenance sessions for a further seven months.

The primary outcome measures are the quality of life of people with dementia, as assessed by QoL-AD, and their care-givers' mental health as assessed by the GHQ-28. Secondary outcomes include: the autobiographical memories of people with dementia; the quality of the relationship between them and their care-givers; and the levels of depression and anxiety felt by them and their care-giver. Using a 5% significance level, comparison of 200 pairs attending joint reminiscence groups with 200 pairs receiving usual treatment will yield 80% power to detect a standardised difference of 0.38 in the QoL-AD rated by the person with dementia and 0.28 in the GHQ-28 or carer-rated QoL-AD. The trial will include a cost-effectiveness analysis from a public sector perspective.

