f) General quality of life of both care-giver and person with dementia, using *EQ-5D *[31]. This is a standard measure of health-related utility, applicable to all health conditions. It provides a simple health profile and a single value for health status designed to calculate Quality Adjusted Life Years (QALYs). Care-givers will complete the measure from their own perspective and for the person with dementia, who will also complete it whenever possible.

g) Functional ability of person with dementia, using the *Bristol Activities of Daily Living Scale *[32], a 20-item scale completed by the carer.

h) Costs, using the validated *Client Services Receipt Inventory *(CSRI) [33]. Used extensively in studies of mental health and dementia (e.g. [34]), this gathers comprehensive data on accommodation, medication and services received. In this trial the data will reflect either the previous three months (at baseline and after treatment) or seven months (at follow-up).

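### The cost list puts lost productivity and carers' session attendance into an analysis declared to be from the public sector perspective, and no other analysis is named to carry them

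*Protocol article*

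**What the plan says.** The Abstract states the perspective: "The trial will include a cost-effectiveness analysis from a public sector perspective". The Cost data section repeats and defines it: "This analysis takes a public sector perspective spanning the NHS (dementia services, primary and secondary care) and local government".

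The same section then introduces the items to be valued: "We shall use national unit costs [38,39] to convert service use to monetary costs, including". Four bullets follow:

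- the cost of running the joint groups;
- the cost of the maintenance groups;
- "direct costs of all health care used by participants in the intervention and control arms of the study";
- "indirect costs of lost productivity and care-givers attending group sessions".

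A closing line excludes intangible costs. On data sources the section says: "We shall estimate the costs of dementia care through the validated CSRI, completed by the family care-giver". Of that inventory, the Secondary outcome measures section says that "this gathers comprehensive data on accommodation, medication and services received".

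The Incremental Cost-effectiveness Analysis section builds the ICER and the cost-effectiveness acceptability curve (CEAC) from costs and effects, without defining the cost set more narrowly.

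**The concern.** A perspective decides whose costs count. With the NHS and local government as payers, a carer's lost earnings, an employer's lost output and a carer's hours at a group session lie outside the numerator. The fourth bullet puts them in.

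The principal economic result is therefore defined in two incompatible ways. An analyst who follows the perspective sentence and one who follows the bullets would produce different ICERs and CEACs, and both could claim to have followed the protocol. If this is left open until the data are seen, the cost set can be chosen with the results known. The discrepancy also has a known direction for one component, because only intervention carers attend sessions.

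**Working it through.** The plan states no figure that could be reproduced here. The check compares the sections and adds one short calculation of hours.

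**Step 1: who bears each listed cost**

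| Listed item | Borne by | Inside the declared perspective? |
|---|---|---|
| Running the joint groups | Local dementia services | Yes |
| Maintenance groups | Local dementia services | Yes |
| Health care used in both arms | NHS | Yes |
| Lost productivity | Workers, households, employers | No |
| Carers' attendance at sessions (read as their time) | Carers | No |

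The lead-in to the list speaks of converting service use into money. Neither item in the last two rows is use of a public service.

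**Step 2: whether another section takes these items out of the principal analysis**

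- Economic Analysis: names cost-effectiveness as the principal method and plans a cost-consequence analysis covering all costs and effects. It does not allocate the fourth bullet to either.
- Incremental Cost-effectiveness Analysis: refers to costs without a narrower definition.
- Sensitivity analysis: the example given varies the time horizon, not the perspective.
- Cost-Consequence Analysis: promises a wider range of costs, but does not say that productivity or carer time belongs there and not in the ICER.

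No section makes the allocation. The items stand in the same list as programme and health care costs, and that list closes with an explicit exclusion, so the natural reading is that they are included.

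**Step 3: direction and amount of carer session time**

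Inputs: 12 two-hour sessions (Intervention); monthly maintenance for seven further months (Abstract), taken as seven sessions; usual care only for controls (Design). The length of a maintenance session is not stated and is assumed to be 1 to 2 hours. Full attendance is assumed.

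- Weekly phase: 12 × 2 h = 24 h
- Maintenance, low: 7 × 1 h = 7 h; total 24 + 7 = 31 h
- Maintenance, high: 7 × 2 h = 14 h; total 24 + 14 = 38 h
- Control arm: 0 h of trial sessions

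Valuing this time at any positive rate raises the incremental cost. Because the Intervention section expects some carers to miss sessions, these hours are upper values for their session lengths.

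**Step 4: what cannot be computed**

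The article gives no hourly value for time, no programme cost, no expected cost difference and no employment data. It does not say whose productivity is meant or how its loss would divide between the arms. The shift in the ICER therefore cannot be calculated.

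**The case against.** The strongest defence is that inclusion in the principal ICER is implied and not stated. The cost-consequence analysis is meant to describe all costs for people with dementia and their carers, and the fourth bullet could have been written with that analysis in mind. This is a fair account of what may have been intended. It does not remove the contradiction, because the bullet sits under the perspective sentence and nothing redirects it.

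A reader might also infer more than the article supports:

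- **That local government care is left out.** The bullets name no social care or accommodation. But the list is open-ended, local government is part of the stated perspective, and the inventory collects accommodation and services. The wording is incomplete; omission is not shown.
- **That the plan breaks its own rule on equal treatment.** The remark that "it is especially important to treat these groups identically when costing" closes a discussion of self-report against GP records and concerns costing method. A resource used in one arm only is a legitimate incremental cost, as the group running costs show. Carer time is a problem because of the perspective.
- **That the whole bullet counts against the intervention.** This holds for session time. Carers in either arm could lose work, and if the intervention reduced such losses, that component would favour it.
- **That the main expected saving is missed.** The Background links relationship breakdown to placement in care and mentions public spending, but it does not rank savings.
- **That the item could reverse the sign of the cost difference.** At an assumed 5 to 15 pounds per hour, session time would come to between 24 × 5 = 120 and 38 × 15 = 570 pounds per intervention pair. Without a programme cost or an expected difference to compare this with, no conclusion about sign follows. The remark that costs and effects may be modest is made in the cost-utility section, to explain a large standard error.

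**Conclusion.** The inconsistency is real and is wrong as written. Two kinds of cost outside the declared perspective are listed for valuation, and no section assigns them to another analysis, so following the text gives a principal ICER and CEAC of mixed perspective.

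The part that can be sized is carer session time: 24 hours per intervention carer in the weekly phase, or about 31 to 38 hours with maintenance, and none for controls. The larger range rests on seven maintenance sessions of 1 to 2 hours and on full attendance. It also rests on reading the attendance item as carers' time. The direction for lost productivity and the effect on the ICER remain undetermined. The clinical endpoints, the randomisation and the power calculation are unaffected.

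**What to change.** Before analysis, state that the base-case numerator for the ICER and CEAC contains NHS and local government costs only. Move lost productivity and carers' session time to a societal-perspective sensitivity analysis labelled as such, or to the cost-consequence analysis. The alternative is to keep the list and change the declared perspective in both the Abstract and the Cost data section; either route removes the contradiction.

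For clarity only, add local-authority social care and publicly funded accommodation, taken from the service-use inventory, to the bullets.

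The cost is a revision of one list and one extra analysis run. Facilitators already complete attendance forms after each session, so session attendance needs no new data collection.

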#### Effectiveness data

We shall evaluate effectiveness through the primary clinical outcomes – QoL-AD, the dementia-specific measure of quality of life and the carer-specific GHQ-28 – both at the primary end-point of 10 months.

#### Incremental Cost-effectiveness Analysis

Incremental cost-effectiveness ratios (ICERs) will summarise changes in the costs and effects of improving quality of life of people with dementia and stress in their care-givers through joint reminiscence group therapy followed by reminiscence-based maintenance, compared with usual care. We shall use bootstrapping to characterise the uncertainty in the cost-effectiveness analysis by estimating the probability distribution of ICERs and generating cost-effectiveness acceptability curves (CEACs) to quantify and display that uncertainty. Though CEACs are widely used in economic evaluation of health care technologies [40], they are no less useful in the evaluation of psycho-social interventions.

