#### Sample size

Our target sample size is 400 patients completing data collection for the trial after ten months, comprising 200 randomised to attend reminiscence groups and 200 receiving treatment as usual. In the trial platform intra-class correlation coefficients (ICCs) within randomised groups were often negative, but never significantly greater than zero, for both the carer-specific GHQ-28 and the carer-rated QoL-AD. However they were close to 0.1 for the QoL-AD rated by the person with dementia. Using a 5% significance level, therefore, comparison of the 200 pairs completing the intervention with the 200 pairs receiving treatment as usual will yield 80% power of detecting a standardised difference of 0.28 in carer-specific GHQ-28 or carer-rated QoL-AD. In contrast the patient-rated QoL-AD is likely to suffer a 'variance inflation factor' of approximately 1.74 [viz. 1 + 0.1 × (average completed group size of 8.4 minus 1)], thus yielding a power of 80% of detecting a standardised difference of 0.38. Our trial platform, which had a sample size of 57 in 3 centres, suggests that standardised differences of 0.28, even 0.38, are plausible. In our judgement they also fall within the range of clinically important effects. Furthermore, because our trial platform was exploratory, and therefore more heterogeneous than the proposed definitive trial, ICCs and standard deviations are likely to fall. To achieve a sample size of approximately 400, we allow for 12% attrition between recruitment and the post-treatment assessment (estimated from our trial platform) and a further 18% attrition over the following 7 months (estimated from a community study [35]). Hence we seek an initial sample size of 576, requiring 24 treatment groups initially comprising 12 pairs and another 288 pairs randomised to usual treatment.

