#### Secondary Cost-Utility Analysis

We shall conduct an exploratory cost-utility analysis using EQ-5D to calculate QALYs for carers and people with dementia, if necessary by getting carers to complete the EQ-5D 'by proxy' for people with dementia [41,42]. The addition of EQ-5D to interview schedules for both care-givers and people with dementia will enable us to estimate and potentially combine the health utility gains to both people with dementia and their carers. This responds to the recommendations from NICE to include utility measures in trials of new drugs and interventions to facilitate cost per QALY calculation and consider the health effects of an intervention regardless of who receives them: "For the reference case, the perspective on outcomes should be all direct health effects whether for patients or, where relevant, other individuals (principally carers)" [43]. Dixon et al have recently highlighted the potential influence on cost per QALY ratios of adding the health utility gains of carers to those of people with conditions like dementia [42]. Given the findings of the trial platform, we predict that both the costs and effects of reminiscence therapy may be modest, with the result that the cost per QALY ratio may have a large standard error. Added to our concern about using a generic measure of quality of life for people with dementia, this leads us to label the cost-utility analysis as secondary to the cost effectiveness analysis.

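### The bootstrap distribution of ICERs, one of two planned displays of economic uncertainty, cannot be interpreted if replicates cross zero effect; incremental net benefit from the same replicates would be safer

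*Protocol article*

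**What the plan says.** The section Incremental Cost-effectiveness Analysis makes the ratio the summary measure: "Incremental cost-effectiveness ratios (ICERs) will summarise changes in the costs and effects". Uncertainty is to be characterised by bootstrapping, with two products: "estimating the probability distribution of ICERs and generating cost-effectiveness acceptability curves (CEACs) to quantify and display that uncertainty". Net benefit is not named, and nothing is said about replicates with a zero or negative effect difference. The Sensitivity analysis section carries both ICERs and CEACs forward.

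The effect measures for this principal analysis are QoL-AD and GHQ-28, "both at the primary end-point of 10 months" (Effectiveness data).

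The Secondary Cost-Utility Analysis section says "we predict that both the costs and effects of reminiscence therapy may be modest", and infers that "the cost per QALY ratio may have a large standard error". It gives this as one reason for ranking the cost-utility analysis below the cost-effectiveness analysis.

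**The concern.** An ICER is a cost difference divided by an effect difference. If the bootstrap effect difference can fall on either side of zero, two things go wrong.

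- **Moments.** Replicates with a denominator close to zero give arbitrarily large ratios of either sign. The ratio then has no stable mean or standard error, and the values obtained depend on which replicates happen to be drawn.
- **Ordering.** A negative ratio can mean cheaper and better, or dearer and worse. A positive ratio can mean dearer and better, or cheaper and worse. Sorting such values does not rank them by value for money, so percentiles of the distribution have no usable meaning.

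At stake is whether one of the two planned displays of economic uncertainty can be read if the observed effect turns out small.

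**Working it through.** Effects are oriented so that positive means benefit (GHQ-28 falls with improvement).

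**1. Reproduce the plan's figures.** From the Sample size section: 200 v 200 completers, 5% significance (taken as two-sided), "80% power of detecting a standardised difference of 0.28 in carer-specific GHQ-28 or carer-rated QoL-AD", and 80% power at 0.38 for patient-rated QoL-AD with variance inflation 1 + 0.1 × (8.4 − 1) = 1.74.

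- GHQ-28: SE = √(2/200) = 0.100. Detectable difference = (1.960 + 0.842) × 0.100 = 0.280. This reproduces.
- QoL-AD: SE = √(2 × 1.74/200) = 0.132. Detectable difference = 2.802 × 0.132 = 0.370, against 0.38 stated (power at 0.38 is 82.1%). The stated figure is slightly conservative and the gap does not matter here. Working back from the stated 80% at 0.38 gives SE = 0.38/2.802 = 0.136.

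**2. Share of replicates at or below zero effect.** Replicates centre on the observed estimate, so if the *observed* effect is d the share is Φ(−d/SE).

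| Observed d | GHQ-28, SE 0.100 | QoL-AD, SE 0.132 | QoL-AD, SE 0.136 |
|---|---|---|---|
| design value (0.28 or 0.38) | 0.3% | 0.2% | 0.3% |
| 0.20 | 2.3% | 6.5% | 7.0% |
| 0.10 | 15.9% | 22.4% | 23.0% |

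**3. Chance that the trial lands in the problem region.** The observed estimate itself varies. If the 95% effect interval reaches zero, at least 2.5% of replicates are at or below zero and the 95% percentile range of the ICER mixes quadrants. If the *true* effect is d, this happens with probability Φ(1.960 − d/SE).

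| True d | GHQ-28, SE 0.100 | QoL-AD, SE 0.132 | QoL-AD, SE 0.136 |
|---|---|---|---|
| design value (0.28 or 0.38) | 20% | 18% | 20% |
| 0.20 | 48% | 67% | 69% |
| 0.10 | 83% | 89% | 89% |

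The 20% is simply the complement of the stated 80% power. If variance inflation applies to the intervention arm only, SE = √((1.74 + 1)/200) = 0.117. The QoL-AD chances are then 10%, 60% and 87%, and the step 2 shares are about 4% at 0.20 and 20% at 0.10.

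**4. Illustration of the consequence.** The documents give no cost figures. The following are assumed: incremental cost 1 unit with SE 0.3, threshold λ = 6 cost units per SD of effect, independent normal cost (C) and effect (E) differences, QoL-AD SE 0.132, 400,000 draws.

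| Observed d | 95% percentile range of C/E | P(λE − C > 0) | P(C/E < λ), quadrant ignored |
|---|---|---|---|
| 0.38 | 0.9 to 8.6 | 0.93 | 0.94 |
| 0.20 | −31 to 45 | 0.59 | 0.66 |
| 0.10 | −88 to 94 | 0.32 | 0.54 |

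At d = 0.10 the mean ICER over blocks of 5,000 replicates ran from about 4 to 208, while the SD of net benefit stayed near 0.85 in all three rows. The gap between the last two columns at d = 0.10, 0.54 − 0.32 = 0.22, is the share of dearer-and-worse replicates. Their negative ratios fall below any positive threshold.

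**The case against.** The best defence is that the quoted sentence promises acceptability curves as well, and the section goes on to defend their use. A curve computed as the proportion of replicates with λE − C > 0 at each threshold is the net-benefit summary in substance. Detail on how it is computed commonly belongs in an analysis plan, which is not shown here. This stands: a reader might infer that the plan rests its uncertainty on the ICER distribution alone, or that its curves will be read off ordered ratios, but the document says neither. The last column of the illustration therefore shows a conditional harm, not a planned one.

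A reader might also infer that the plan itself expects an effect near zero. It does not. The word used is modest, it appears in the cost-utility section, and the conclusion about a large standard error is drawn only for cost per QALY. For the primary outcomes the Sample size section calls 0.28, even 0.38, plausible. If the observed effect equals those values, only 0.2–0.3% of replicates fall at or below zero and the ICER percentiles are usable.

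The plan also ranks the cost-utility analysis second, adds a cost-consequence analysis that uses no ratio, and names no mean or percentile interval for the ICER.

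What the defence does not remove is that the ICER distribution remains a named output of the principal analysis. The reassurance at the design values also requires the observed effect to equal the design value; step 3 shows how often it would fall short.

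**Conclusion.** The point holds as a cheap improvement, not as the correction of a wrong figure or a contradiction. One of the two planned products, the bootstrap distribution of ICERs, becomes uninterpretable when replicates cross zero effect. On the plan's stated power, that would affect a 95% summary in about 20% of trials even at the design effects, and in roughly half to two-thirds (48% to 69%) at a true standardised effect of 0.20. The other product, the acceptability curve, is sound if built from joint differences.

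This rests on approximately normal replicates centred on the observed estimate, with the precision the Sample size section implies. The effects 0.10 and 0.20 are assumed values for what modest might mean, and the cost figures in step 4 are illustrative only. No figure in the documents allows the same calculation for QALYs.

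**What to change.** In the economic analysis text:

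- Bootstrap the pair (cost difference, effect difference).
- Replace the ICER distribution with incremental net benefit and its confidence interval over a range of willingness-to-pay thresholds.
- State that the CEAC is the proportion of replicates with positive net benefit at each threshold.
- Show the replicates on the cost-effectiveness plane.
- Report the ICER as a point estimate, with no mean, standard error or percentile interval when replicates cross zero effect.

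The data and the replicates are unchanged, so the cost is wording. The drawback is that the answer is quoted over a range of thresholds instead of as a single ratio with an interval.
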